### Stage 3: Acceptability, Feasibility, and Scalability of FOCUSau (Objective 4)

Our approach is underpinned by a conceptual framework that highlights the link between acceptability, fidelity and feasibility, and potential implementability [66]. An investigation of fidelity will also inform internal validity and thus our interpretation of the effectiveness findings. If prospective acceptability, uptake and engagement with the intervention are moderate (based on conventional cutoff scores of 50%) [67,68], then FOCUSau is feasible to deliver in other settings; if participants receive and comprehend FOCUSau as designed (ie, fidelity is high), then the effectiveness findings will represent a valid test of the intervention; if participant retention and retrospective acceptability are high, then FOCUSau is likely to be maintainable; and if FOCUSau is cost-effective and additional workforce requirements are minimal, then the intervention is likely to be scalable. Acceptability is “the extent to which people receiving FOCUSau consider it to be appropriate, based on anticipated (prospective) or experienced (retrospective) cognitive and emotional responses to the intervention” [69]. Informed by a new and influential theoretical framework of acceptability [69], we will pilot test a questionnaire [44] to be administered at baseline and follow-up (T_0_ and T_2_). As acceptability is ideally assessed both quantitatively and qualitatively [36], a diverse subsample of participants (~30 dyads) will be recruited from the intervention group and be interviewed via videoconference immediately following the completion of FOCUSau (T_1_), to gain a greater insight into intervention acceptability, including potential for further enhancements. As for the uptake, we will document the recruitment process, including reasons for accepting or declining participation and examine the sociodemographic profile of dyads invited to participate in the trial, capturing our capacity to reach relevant populations (with lower socioeconomic status, cultural minorities, and from rural or remote locations). We will also use the aforementioned T_1_ interviews to explore barriers and enablers to uptake by dyads. Interview topic guides (1 for patients; a parallel guide for caregivers) will be informed by the TDF of behavior change [65]. Intervention fidelity encompasses whether the intervention is delivered and received as planned [70]. We will document communication between trial managers and participants, whether for technical problem-solving or for other reasons, to assess whether components have been added to FOCUSau as designed. Aspects of adherence (intervention as received) are built into the FOCUSau internet module and include a readily accessible “help” function. Dyads who experience problems with onboarding for the FOCUSau sessions will receive help from the trial manager via phone; they will confirm their presence and indicate whether they are using the computer or phone; dyads who exit an FOCUSau session before completion will be sent a reminder email or text message. Completion rates of individual FOCUSau sessions will be monitored.

The audiotaped semistructured interviews with dyads to assess FOCUSau acceptability will be transcribed verbatim and thematically analyzed using the Framework method [46]. To ensure methodological rigor, the analysis will follow (1) a step-by-step guide outlined by Gale et al [71] and (2) criteria for trustworthiness [72]. The deductive analysis will be informed by the theoretical framework of acceptability (component constructs—affective attitude, burden, ethicality, intervention coherence, opportunity costs, perceived effectiveness, and self-efficacy) ascertaining whether particular elements of FOCUSau were experienced as positive or negative and will include themes from previous intervention evaluations. Coding of established themes and subthemes will be computer-assisted using NVivo software (Lumivero). Statistical descriptions of the quantitative data from the intervention checklist and routine monitoring will be used to describe fidelity, using conventional cutoff points for acceptable intervention adherence.

For technical aspects of implementability we will consider key factors in the scalability, that is “the ability of a health intervention shown to be efficacious on a small scale or under controlled conditions, to be expanded under real-world conditions to reach a greater proportion of the eligible population, while retaining effectiveness” [73]. This study will follow the previous stages and will be the subject of additional human research ethics approval. It will use health IT expert consensus methods, to determine the technical feasibility of implementing and operating the FOCUSau program as an ongoing service at each site that is participating in the clinical trial, as well as at other potential hosting sites for the program that are identified during the clinical trial. The assessment of this aspect of implementability [66] will entail either semistructured interviews or focus groups with health IT stakeholders who may include trial managers, software proprietors, digital health specialists in health service management and governance roles, and experts in the deployment of software in routine clinical care. The interview or focus group schedule will use two probes which are (1) a technical specification of the software as it has been adapted for use in the trial, based on work done by the proprietor with the research computing services group and (2) a summary of the intervention’s clinical and socioeconomic value proposition, based on preliminary findings of project studies up to this point. The interview or focus group schedule will collect and thematically analyze data, based on stakeholders’ knowledge of current local, national and international best practice approaches to digital health implementation planning [74,75], including the Australian Digital Health Agency technical standards and specifications.

### Data Management, Monitoring, and Risk Management

CST has a suite of standard operating procedures that will be used in support for the management of study data including electronic data handling, case report forms, archiving of research materials, and record destruction. Referral and recruiting reviews will be undertaken via monthly trial management video calls and ongoing oversight by the lead investigator. Monitoring will be conducted remotely, including data quality, protocol deviations or violations, adverse event reporting, participant consent, and eligibility. We will also monitor recruitment status and target achievement, review any adverse events or serious adverse events (suspected or actual), and review participant withdrawals and mortality.

### Ethical Considerations

This research protocol was approved by the Human Research Ethics Committee of St Vincents Hospital Melbourne (ERM ID 84479, SAGE Project ID 2022/PID06577, and SVHM Local Ref ID 262/22). FOCUSau is noninvasive with no known risk of protocol-related injury. As a psychoeducational intervention focused on the provision of information we anticipate the risk of any adverse events to be low. Nevertheless, information is available in FOCUSau about where participants may access additional medical and psychosocial support. Our project team is experienced in leading complex psychosocial interventions involving the recruitment of patients with advanced disease and their family caregivers. If necessary, any adverse events will be reported to the CTS Ethical and Data Monitoring Committee. Due to the nature of the study population, some deaths due to advanced disease progress are expected. A protocol for liaising with the caregiver of the deceased has been developed for these situations. This includes advising caregivers allocated to the intervention arm that they will not be required to continue with the study.

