#### Data Collection: Primary and Secondary Psychosocial Outcomes

Patient-caregiver dyad data will be collected at 3 time points—baseline (T_0_) completed prerandomization, first follow-up (T_1_) at 12 weeks post baseline, and second follow-up (T_2_) at 24 weeks post baseline. All data will be completed by the dyads (regardless of allocation) using the FOCUSau software platform, whereby they will complete a suite of internet-based questionnaires. The platform enables the application of data validation rules to ensure that required data are entered or that an annotation is provided to explain any missing data. The FOCUSau platform automatically generates a unique ID number used by the dyad to log into the platform. Data collection will be completed separately by the patient and caregiver (regardless of allocation). The data collection points, outcomes, and measures have been selected in accordance with those used in the aforementioned EU trial to enhance international comparison and potential generalizability [39].

The list of variables and associated measures to be completed by the dyad are summarized in Table 1 and are as follows, for the primary outcomes—emotional well-being (10 items describing emotional functioning from the European Organization for Research and Treatment of Cancer (EORTC) The European Organisation for Research and Treatment of Cancer Core Quality of Life Questionnaire (QLQ-C30) [55,56] and self-efficacy (The Lewis’ Cancer self-efficacy scale [57]); for the secondary outcomes—QoL of patients—EORTC QLQ-palliative care [58], 2 social functioning items (#26, 27) plus 1 item about overall health (#29) from the EORTC QLQ-C30, social well-being scale from Functional Assessment of Cancer Therapy-General (FACT-G)—and family caregivers (The Caregiver Quality of Life Index-Cancer [59]), appraisal of illness (Benefits of illness scale [60]), coping (Brief cope [61]), and dyad communication (Ways of giving support questionnaire [62] plus 1 item from the Dyadic Coping Inventory).

In addition, we will administer a sociodemographic questionnaire at baseline (T_0_) and a modified version of the Eastern Cooperative Oncology Group (ECOG) Performance Status Assessment [63] (response option 5 “death” removed as not relevant for this study).

**Table 1 table1:** Trial data collection measures.

Objective and outcome or variable			Instrument	Timing		
				T_0_: Before randomization	T_1_:T_0_ + 12 weeks	T_2_: T_0_ + 24 weeks

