#### Data Analysis

The effectiveness of FOCUSau will be compared with the standard care (control group) for each participant population (patients or caregivers). Our hypotheses will be tested using a mixed model (per participant population) with the T_1_ measurement values for emotional well-being and self-efficacy as primary outcomes using a significance level of α=.025. These mixed models will be implemented using SPSS (IBM Corp) for Windows (version 27.0; Microsoft Corp) and R (R Core Team) with the recruitment centers treated as a random effect and the randomization groups as predictor variables. As per the FS procedure, the null hypotheses of the second primary end point (self-efficacy) will only be tested if a significant result is found for the first primary end point (emotional well-being). Additionally, we will incorporate other factors identified in the literature as potentially predictive by including them as covariates in the mixed models. We will perform analyses on both “intention-to-treat” and per-protocol principles. To interpret the magnitude of the effects for the different outcomes, we will estimate effect sizes (Cohen *d*). Our analysis will encompass all primary and secondary outcomes. Primary end points, including emotional well-being and self-efficacy measured at T_1_, will be analyzed first. Following that, secondary end points, comprising outcomes measured at T_1_ that are not primary end points, as well as all outcomes measured at T_2_ (occurring 24 weeks from T_0_), will be assessed. This approach allows for a comprehensive evaluation, including the examination of longer-term effects.

The robustness and validity of the results will be explored using sensitivity analyses by varying the parameter inputs (including sensitivity to the use of values for missing observations). The analysis will be conducted within trial period; the potential to extrapolate results over the longer term will be assessed based on the proportion of patients alive at the end of follow-up.

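### The article states a release from the study after a patient's death for intervention-arm caregivers and none for controls, so bereaved caregivers may be lost unevenly and the caregiver comparison may favour the intervention

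*Protocol article*

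**What the plan says.** Ethical Considerations says that "Due to the nature of the study population, some deaths due to advanced disease progress are expected" and that "A protocol for liaising with the caregiver of the deceased has been developed for these situations". That procedure is not shown. One element of it is given: "This includes advising caregivers allocated to the intervention arm that they will not be required to continue with the study". The sentence is conditioned on allocation, and the release it describes is from the study as a whole, not from the sessions. Control-arm caregivers are not mentioned.

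Three other statements bear on this.
- Data Collection: Primary and Secondary Psychosocial Outcomes: "All data will be completed by the dyads (regardless of allocation) using the FOCUSau software platform". Patient and caregiver answer separately.
- Data Analysis, on the primary comparison: "Our hypotheses will be tested using a mixed model (per participant population) with the T_1_ measurement values for emotional well-being and self-efficacy as primary outcomes". Caregivers therefore have their own primary comparison.
- Data Analysis, on the analysis sets: "We will perform analyses on both “intention-to-treat” and per-protocol principles".

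For missing data, Data Analysis foresees likelihood methods where data can be taken as missing at random, and sensitivity analyses that vary the values used for missing observations. Data Management, Monitoring, and Risk Management lists withdrawals and mortality among the items under review.

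**The concern.** Caregiver emotional well-being and self-efficacy at T1 are primary outcomes. A caregiver whose patient has just died may well score lower, at least on emotional well-being. If staff tell such caregivers in one arm that they may leave the study, and the same message is not given in the other, fewer low scores may be collected in the intervention arm than in the control arm. That would make the intervention look better than it is. Deaths accumulate, so T2 is more exposed than T1.

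An intention-to-treat comparison needs follow-up that does not depend on allocation. A release that covers the questionnaires and is worded for one arm does not fit that aim. Recruitment began in July 2024, and a T1 questionnaire that was never offered cannot be recovered later.

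**Working it through.** **Inputs from the article.** 173 dyads per arm, α = 0.025 and a planned difference of 0.375 SD (Sample Size). The article does not give the sidedness of α; I take it as two-sided. It has no figure of its own on bereavement to reproduce. I use 173 only as the number analysed per arm. Whether 173 follows from the stated design inputs is a separate question and does not affect the bias below.

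**Inputs that are assumptions.** The article gives none of these:
- m, the share of patients who die before T1, taken as equal in both arms: 5% to 20%.
- D, the deficit of bereaved caregivers in SD units: 0.3 to 1.0.
- ri and rc, the fractions of bereaved caregivers who still respond in the intervention and control arms.

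Non-bereaved caregivers are assumed to respond alike in both arms, and the true intervention effect is set to zero.

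**Bias.** Among responders, the bereaved share is f(r) = m·r / (m·r + 1 − m). The complete-case bias towards the intervention is D × [f(rc) − f(ri)].

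Worked case, m = 10%, D = 0.5, ri = 0.5, rc = 0.8:
- f(0.8) = 0.08/0.98 = 0.0816
- f(0.5) = 0.05/0.95 = 0.0526
- bias = 0.5 × 0.0290 = 0.015 SD

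With ri = 0 and rc = 1 the formula reduces to m × D. With ri = rc it is zero.

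**False-positive rate.** SE = √(2/173) = 0.1075 SD, and the two-sided critical value at 0.025 is 2.241. The rejection probability under no effect is 1 − Φ(2.241 − bias/SE) + Φ(−2.241 − bias/SE). For a bias of 0.10, bias/SE = 0.930 and the result is 0.0956. This is a normal approximation without covariates and takes 173 analysed in each arm.

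Bias in SD, with the false-positive rate in brackets:

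| m | D | ri 0.5, rc 0.8 | ri 0, rc 0.5 | ri 0, rc 1 |
|---|---|---|---|---|
| 5% | 0.3 | 0.004 (2.5%) | 0.008 (2.5%) | 0.015 (2.6%) |
| 10% | 0.5 | 0.015 (2.6%) | 0.026 (2.9%) | 0.050 (4.1%) |
| 10% | 1.0 | 0.029 (3.0%) | 0.053 (4.3%) | 0.100 (9.6%) |
| 20% | 0.5 | 0.028 (3.0%) | 0.056 (4.5%) | 0.100 (9.6%) |
| 20% | 1.0 | 0.056 (4.5%) | 0.111 (11.4%) | 0.200 (35%) |

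In the last column, m = 15% with D = 1.0 gives 0.15 × 1.0 = 0.15 SD and a rate of 20%.

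Against the planned 0.375 SD, the milder split runs from about 1% (0.004/0.375) to 15% (0.056/0.375). A bias of 0.15 SD is 40% (0.15/0.375) and 0.20 SD is 53% (0.20/0.375).

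**Missing at random.** Different response rates by arm do not by themselves break this assumption, because arm is in the model. The difficulty is that the death happens after baseline and can drive both non-response and the score. A likelihood analysis with arm, centre and baseline covariates that ignores the death would not reliably remove the bias. Using the death in the model could help, provided some bereaved intervention caregivers respond. If none do, that arm holds no information on their scores.

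**The case against.** The strongest reply is that the sentence is one item from a fuller bereavement procedure that is not shown. That procedure may give controls the same message. The intervention arm may be singled out simply because only its caregivers have joint sessions left, and those cannot be done together after a death. This stands. A reader might infer that only intervention caregivers are released and that control questionnaires continue, but the article does not say so; that reading rests on silence about controls.

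A reader might also infer that bereaved caregivers leave the data in one arm only, so that the comparison is biased. The text does not support that either. Being told one need not continue is permission, not removal. Nothing says that data are discarded or that a willing caregiver is refused a questionnaire, and bereaved controls may stop too.

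The tension with data collection in both arms is loose. That wording describes how and by whom questionnaires are completed, not what follows a death. The article also monitors mortality and withdrawals, plans sensitivity analyses for missing values, and limits likelihood methods to data that can be taken as missing at random.

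What the reply does not remove is the wording itself. The stated release is tied to allocation and reaches beyond the sessions. Staff who follow it literally would treat the arms differently with respect to a primary caregiver outcome.

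**Conclusion.** The point holds as a risk created by stated text, not as a demonstrated bias. As worded, the release may lose more bereaved caregivers from the intervention arm. If they score worse, the caregiver comparison may be shifted towards the intervention at T1, and more so at T2.

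The size cannot be fixed from the article. It is zero if both arms are handled alike and about 0.004 to 0.056 SD under a 50% against 80% response split. Values of 0.15 SD or more, with false-positive rates of 20% and above, require no response from bereaved intervention caregivers, full response from bereaved controls, and high values of both m and D. They mark the upper end and are not an expectation. For self-efficacy the effect of bereavement is a further assumption.

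If the procedure that is not shown already treats both arms alike, one clarifying sentence settles the matter.

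**What to change.** Reconcile Ethical Considerations with the intention-to-treat aim in Data Analysis and with data collection in both arms.
- State release from the sessions separately from data collection.
- Give bereaved caregivers in both arms the same offer, in the same words, to complete or decline the T1 and T2 questionnaires.
- Report by arm the number of bereaved caregivers and how many responded at each time point.
- Add a sensitivity analysis that treats bereaved caregivers identically in both arms, for example by excluding them from both. This addresses the narrower question of caregivers whose patient is alive, and it assumes that the intervention does not affect survival. It also covers caregivers already released under the present wording.

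The cost is a change to the contact script and an ethics notification. The downside is that some bereaved caregivers will be offered a questionnaire they may decline.

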## Results

This study was funded in March 2022 and recruitment commenced in July 2024.

## Discussion

### Anticipated Principal Findings

Australia’s capacity to meet its national palliative care standards has been challenged [10]. This project will examine the clinical and health economic impacts of FOCUSau and gauge its potential for maintainability. If shown to be effective, this intervention will improve the emotional well-being of patients with advanced cancer and their family caregivers, regardless of their location or current level of health care support. Empirical findings as described above will inform an implementation and maintainability strategy. The strategy will describe a pathway and recommended steps for longer-term systematic delivery of FOCUSau across Australia, linking where possible with existing nationally supported cancer and palliative care programs.

### Comparison With Prior Research

Historically, much of the psychological and psychoeducational palliative care intervention research has been delivered in person focusing on either the patient or their family caregivers [21,23-25]. However, trials of dyadic interventions, which focus on the patient and family caregiver together, have shown favorable outcomes for both parties [18,20,21]. Furthermore, digital health interventions offer an innovative modality and may provide considerable resource advantages to in-person interventions [26,27]. Hence, our trial will advance knowledge in these areas.

### Limitations

We acknowledge some of the limitations associated with our control arm, including that control participants will not have access to FOCUSau after the final data collection point. Unfortunately, we do not have the funding and resources required to support this. We will, however, report on the number of participants who withdraw because they have not been allocated to the intervention arm.

### Conclusions

Advanced cancer is a “family affair” significantly affecting the well-being of the person with cancer and their family [1]. We seek to determine the effectiveness and maintainability of a digital health intervention (FOCUSau) aimed at improving the well-being of patients with advanced cancer and their primary family caregivers.

## Abbreviations

CSRI: Client Services Receipt Inventory
CST: Cancer Symptoms Trials
ECOG: Eastern Cooperative Oncology Group
EoL: end of life
EORTC: European Organization for Research and Treatment of Cancer
EU: European Union
FACT-G: Functional Assessment of Cancer Therapy-General
FOCUS: Family, Outlook, Communication, Uncertainty, Symptom management
FOCUSau: Family, Outlook, Communication, Uncertainty, Symptom management in the Australian context
FS: fixed sequence
iFOCUS: digital Family, Outlook, Communication, Uncertainty, Symptom management
QLQ-C30: The European Organisation for Research and Treatment of Cancer Core Quality of Life Questionnaire
QoL: quality of life
REDCap: Research Electronic Data Capture
TDF: Theoretical Domains Framework
